**Methods:**

The FocaL mass drug Administration for *Plasmodium vivax* Malaria Elimination (FLAME) study is a 3-year cluster randomized controlled trial to determine the impact and safety of fMDA to reduce *P. vivax* transmission. The study will be conducted in Loreto, Peru, where standard interventions have reduced *P. vivax* cases, but transmission persists due to a high proportion of subclinical infections. Thirty low transmission communities (API < 250 cases/1000 population) will be randomized 1:1 to fMDA versus control using a restricted randomization. All communities will receive Peruvian national standard malaria control measures. In the intervention arm, high-risk individuals (living within 200 m of a *P. vivax* case reported in the prior 2 years) without contraindication to study medications, including G6PD deficiency, will receive three cycles of fMDA over a 2-year period. Each cycle will include two rounds of directly observed therapy delivered 2 months apart. The fMDA regimen will include 25 mg/kg chloroquine (CQ) plus a single 300 mg dose of tafenoquine (TQ) for individuals age ≥ 16 years, and 25 mg/kg of CQ plus 7 days of 0.5 mg/kg/day of primaquine (PQ) if younger. The primary outcome is the cumulative incidence of symptomatic *P. vivax* malaria. The sample size provides 80% power to detect at least a 68% relative reduction in cumulative *P. vivax* incidence, based on alpha of 0.05 and a coefficient of variation (*k*) of 0.87. Secondary outcomes include safety, cost-effectiveness, and infection prevalence and seroprevalence which will be assessed in annual cross-sectional surveys. Safety will be assessed in passive and active pharmacovigilance, including post-treatment screening for G6PD-associated hemolysis by assessing for anemia and hematuria in a sample.

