#### fMDA in the intervention arm

In the intervention arm, fMDA will be administered over 3 consecutive years. In each cycle, the intervention arm will receive two rounds of fMDA, with each round separated by 2 months and each cycle separated by 9–11 months (Fig. 4). fMDA will be administered by directly observed therapy (DOT) and will target high-risk individuals meeting eligibility criteria detailed in Table 1. These eligibility criteria include being a malaria index case or living in a household within a 200-meter radius of a *P. vivax* index case. The 200-meter radius was selected based on evidence from other cohort studies in the Peruvian Amazon indicating clustering of asymptomatic, submicroscopic infections among neighboring households, generally within 200 meters [33–35]. Index cases will include cases reported in the 2 years prior to the first round of each fMDA cycle detected through passive or active case detection. Individuals with high-risk status will be screened for other inclusion and exclusion criteria for fMDA eligibility.

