**Fig. 4 Fig4:**
[figure not shown]
Schematic of the overall study timeline and major activities including surveys and fMDA. Each activity is demarcated with a colored triangle. The grant period includes annual cycles from June to May (orange bars), and the historic peak transmission season includes the period between November and April (purple bars). Abbreviations: NCE = no cost extension

**Table 1 Tab1:** Eligibility criteria for study activities

	Inclusion criteria	Exclusion criteria
Clusters	• Within 8 h transport of Iquitos • Incidence < 250/1000 and > 2 cases in the year prior to trial • Population size (< 650)	• Outside of study area including villages on the banks of the Momon, Nanay, Itaya, and Pintuyacu rivers and along the main road in the region, Carretera Iquitos-Nauta
Study enrollment	• Slept in household within study community at least one night in the past 4 weeks •$$\geq$$ 6 months old • Signed informed consent	
fMDA		
Chloroquine	• Resides in neighboring household but within 200 m of Pv index case in the past 2 years • Age ≥ 6 months old • Present for intervention • Adult ≥ 18 years old that provides informed consent • A child ≥ 8 years and < 18 years old that provides informed assent and has informed consent from their parents • A child ≥ 6 months old and < 8 years old that has informed consent from their parents	• History of retinal or visual field changes • Known hypersensitivity or adverse reaction to CQ • Currently taking CQ or have taken CQ in the past 4 weeks • Ineligible for TQ or PQ (see criteria below) • Hemoglobin < 9 g/dL
Tafenoquine	• Eligible to receive CQ • Age ≥ 16 years old • Adult ≥ 18 years old that provides informed consent • A child ≥ 16 years and < 18 years old that provides informed assent and has informed consent from their parents	• G6PD deficiency or intermediate status (defined as activity $$\le$$ 6.0 UI/gHb per SD biosensor) • G6PD status unknown or refusal of G6PD status test • Acute or severe malaria • Pregnancy (known or identified by pregnancy test) • Refusal of pregnancy test if new amenorrhea in the past 4 weeks • Woman breastfeeding a child that is G6PD deficient or with unknown G6PD status • Known hypersensitivity or adverse reaction to TQ or PQ • Have taken mefloquine (i.e., artesunate-mefloquine), TQ or PQ, or other antimalarial in the past 4 weeks • Hemoglobin < 9 g/dL

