Primaquine	• Eligible to receive CQ and ineligible to receive TQ • Age ≥ 6 months old • Adult ≥ 18 years old that provides informed consent • A child ≥ 8 years and < 18 years old that provides informed assent and has informed consent from their parents • A child ≥ 6 months old and < 8 years old that has informed consent from their parents	• G6PD deficiency (defined as activity ≤ 4.0 UI/gHb per SD biosensor) • G6PD status unknown or refusal of G6PD status test • Acute or severe malaria • Pregnancy (known or identified by pregnancy test) • Refusal of pregnancy test if new amenorrhea in the past 4 weeks • Breastfeeding child with documented or unknown G6PD deficiency status • Known hypersensitivity or adverse reaction to TQ or PQ • Have taken mefloquine (i.e. artesunate- mefloquine), TQ or PQ, or other antimalarial in the past four weeks • Hemoglobin < 9 g/dL

Each round of fMDA will include CQ plus either TQ, for non-pregnant individuals $$\ge$$ 16 years of age and G6PD normal, or PQ, for non-pregnant individuals 6 months to 15 years of age and G6PD normal or intermediate. The prevalence of G6PD deficiency in the study area is anticipated to be < 5% [36–40]. Preliminary data from the study area shows that 36.2% of the study population is > 6 months and < 16 years and will receive PQ. If pediatric TQ is approved for use in Peru during the study, its use will be incorporated into the study.

For the first annual rounds (referred to as 1a, 2a, and 3a for years 1, 2, and 3, respectively) the regimen will include 3 days of CQ (10 mg/kg on days 1 and 2, and 5 mg/kg on day 3) for treatment of *P. vivax* asexual blood stages, with TQ or PQ for *P. vivax* hypnozoite stages (TQ 300 mg × 1 or PQ 0.5 mg/kg/day × 7 days) (Table 2). PQ and TQ provide prophylactic and gametocytocidal effects against both *P. vivax* and *P. falciparum* [41–45]. However, compared to PQ which has a short half-life of roughly 4–9 h [46–48], TQ will provide an extended period of protection given its prolonged terminal elimination half-life (~ 15 days), the time it takes to reduce the plasma concentration of TQ by 50%. This will provide post-treatment prophylaxis for up to 77 days [49, 50].

**Table 2 Tab2:** Drugs formulations and doses for all fMDA Rounds

**Drug***	**Dosage form (mg)**	**Administration**	**Manufacturer**	**Dose**	
				**≥16 years**	**6 mos – 15 years**

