**Chloroquine (CQ)**					
3-day CQ (Rounds 1a, 2a, 3a)	150 mg base	Take with food to minimize possible gastrointestinal irritation	Kronos Lab, Guayaquil, Ecuador	Dose ~10 mg/kg (D1, D2), ~5 mg/kg (D3)	Dose ~10 mg/kg (D1, D2), ~5 mg/kg (D3)
sdCQ (Rounds 1b, 2b, 3b)				Dose ~10 mg/kg once	Dose ~10 mg/kg once
**Tafenoquine (TQ)** (all Rounds)	150 mg	TQ should be taken with food to increase absorption	Piramal Pharma Ltd, Mumbai, India	300 mg once	n/a
**Primaquine (PQ) **(all Rounds)	15 mg	Take with food	Colompack S.A., Bogota, Colombia	Dose ~0.5 mg/kg daily x 7 days (If TQ is contraindicated)	Dose ~0.5 mg/kg daily x 7 days
*fMDA: focal mass drug administration; CQ: chloroquine; sdCQ: single dose chloroquine; TQ: tafenoquine; PQ: primaquine; D1: Day 1; D2: Day 2; D3: Day 3* **The commercial name of the product and the manufacturer may vary depending on if the product is bought or donated.*					

Coverage and effectiveness of MDA can be compromised by drug eligibility criteria and potential challenges of acceptability, drug efficacy, adherence, imperfect surveillance to identify high-risk individuals, and human movement. Additional rounds of MDA may be needed, particularly in tropical settings where strains cause more frequent relapses in patients. Thus, the fMDA intervention will include second annual rounds (referred to as 1b, 2b, and 3b for years 1, 2, and 3, respectively). 

The regimen will include single-dose CQ (10 mg/kg × 1) with either PQ (0.5 mg/kg/day × 7 days) or TQ (300 mg × 1). CQ, including in a single dose, may potentiate the anti-relapse effect of PQ and TQ [7, 51, 52]. A single dose in the second annual rounds will also facilitate administration and acceptability. Administration of this second round at approximately 2 months after each first annual round will serve to prolong the anti-relapse, as well as providing prophylactic and transmission-blocking activity of fMDA. In multi-site, double-blind, double-dummy, randomized trials comparing TQ to placebo and to PQ [31, 36], efficacy to prevent recurrences was 72.8% (95% CI 65.6–78.8) and 67% (95% CI 61.0–72.3) for PQ and TQ, respectively, at 180 days.

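### The text and the tables disagree on whether G6PD-intermediate people aged 16 or over receive primaquine, and Table 1 omits the index case and own household that the text includes

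*Protocol article*

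**What the plan says.** **Drug by age and G6PD status, text.** Under fMDA in the intervention arm, the sentence after Table 1 assigns TQ to non-pregnant, G6PD-normal people at or above 16, "or PQ, for non-pregnant individuals 6 months to 15 years of age and G6PD normal or intermediate". The abstract describes the under-16 regimen as "25 mg/kg of CQ plus 7 days of 0.5 mg/kg/day of primaquine (PQ) if younger" and gives no PQ option for older people.

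**Drug by age and G6PD status, tables.** The PQ row of Table 1 requires a person to be "Eligible to receive CQ and ineligible to receive TQ". It sets a minimum age of 6 months and no maximum, lists consent for adults of 18 or over, and excludes only G6PD activity at or below 4.0. In Table 2 the PQ entry in the column for ages 16 and over reads "Dose ~0.5 mg/kg daily x 7 days (If TQ is contraindicated".

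**Who is targeted.** The text says that the Table 1 criteria include "being a malaria index case or living in a household within a 200-meter radius of a" *P. vivax* index case. The only residence criterion in Table 1 is "Resides in neighboring household but within 200 m of Pv index case in the past 2 years".

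**The chloroquine (CQ) exclusion.** Table 1 excludes from CQ anyone "Ineligible for TQ or PQ (see criteria below".

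**The concern.** For one group the passages give opposite answers, treat or do not treat. That group bears on the trial's adverse event of special interest, haemolysis associated with 8-aminoquinolines. The safety population, and the exposure behind the halting rule for serious events related to these drugs, therefore depend on which passage is followed.

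The index-case mismatch is of another kind. It affects who counts as targeted, and so the coverage denominators and the per-protocol analysis, which keeps clusters where at least 80% of interventions followed the protocol. It is not a G6PD safety matter.

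**Working it through.** No formula in the plan is in dispute, so the check sets the rules side by side.

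**Step 1: age by G6PD category.** Inputs: the G6PD bands in Enrollment and a baseline assessment (deficient up to 4.0, intermediate 4.1 to 6.0, normal 6.1 or more IU/g Hb), the text after Table 1, and the TQ and PQ rows of Tables 1 and 2. All other criteria are taken as met, and the CQ exclusion is read as ineligible for both drugs.

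| Age | G6PD | Text | Tables 1 and 2 |
|---|---|---|---|
| 6 months to 15 years | normal | CQ+PQ | CQ+PQ |
| 6 months to 15 years | intermediate | CQ+PQ | CQ+PQ |
| 6 months to 15 years | deficient | none | none |
| 16 or over | normal | CQ+TQ | CQ+TQ |
| 16 or over | intermediate | **none** | **CQ+PQ** |
| 16 or over | deficient | none | none |

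Five of six cells agree. The sixth gives the same result at 16 to 17 as in adults. Apart from the G6PD cut-off (6.0 for TQ, 4.0 for PQ), the two exclusion lists are materially the same: pregnancy, haemoglobin, unknown G6PD status, breastfeeding, hypersensitivity, recent antimalarials and acute malaria. The table-only route to PQ at 16 or over therefore opens for G6PD-intermediate people and, in substance, nobody else.

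**Step 2: index case and own household.** The text under fMDA in the intervention arm includes both. Identification of index cases and measurement of incidence makes an enrolled intervention-arm index case eligible at the next cycle. The abstract defines high risk as living within 200 m of a case, which covers the index household. Table 1, to which the text attributes its criteria, has no entry for either. Read literally, the omission applies where no second index case in another household lies within 200 m; otherwise the person qualifies as that case's neighbour.

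**Step 3: the CQ exclusion.** Read as ineligible for either drug, it bars everyone under 16, because TQ requires age 16. PQ needs CQ eligibility together with TQ ineligibility, so nobody could ever receive PQ. Read as ineligible for both, it gives the right-hand column of the table above.

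**Step 4: how many people.** Inputs: 15 clusters per arm and a mean of 251 people per cluster (sample size section); 36.2% of the population older than 6 months and under 16 (text after Table 1).

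- Intervention-arm residents: 15 × 251 = 3,765.
- Aged 16 or over: (1 − 0.362) × 3,765 = 0.638 × 3,765 ≈ 2,402, ignoring infants under 6 months.
- G6PD-intermediate, assumed 2%, 5%, 10%: 2,402 × 0.02 ≈ 48; × 0.05 ≈ 120; × 0.10 ≈ 240.
- As a share of residents: 0.638 × 0.02 ≈ 1.3%; × 0.05 ≈ 3.2%; × 0.10 ≈ 6.4%.

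The prevalence is an assumption: the only G6PD prevalence in the document, below 5%, is for deficiency. The denominator is every resident aged 16 or over. fMDA reaches only those near an index case who are present, consent and meet the other criteria, and that fraction is not given. Each count is thus an upper bound at its assumed prevalence.

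**The case against.** **The text defers to Table 1.** fMDA is said to target people who meet the Table 1 criteria, the two tables agree with each other, and the sentence after Table 1 may be a short summary that leaves out the fallback. This is the strongest reply, and it narrows the conflict to PQ or nothing: no passage gives TQ to intermediates or an 8-aminoquinoline to deficient people. It does not close the point. The abstract repeats the age split, and the text names G6PD-intermediate status for the younger group only. Letting Table 1 prevail throughout would also drop the index case and own household, which the text includes, so no single order of precedence removes both mismatches.

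**The CQ exclusion.** A reader might infer that it empties the PQ group and removes the 36.2% of the population under 16. The document does not support that: it says that this group will receive PQ, and Table 2 has a paediatric PQ column. Only the reading ineligible for both is workable, so the clause needs rewording and nothing more.

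**Delivery in the field.** A reader might infer that teams will treat people differently. That is not shown. The article condenses a fuller Spanish protocol (version 5.6, Trial status), which may hold a clear algorithm.

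**Effect on the analyses.** The primary analysis compares whole clusters as randomised with population as the offset, so its method is untouched. Safety by drug can be tabulated by the drug actually given. Both replies stand. What still depends on the rule is who should have been treated, and hence coverage and protocol adherence.

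**Conclusion.** The point holds as an internal inconsistency. For G6PD-intermediate people aged 16 or over, the text and abstract imply no regimen, whereas Tables 1 and 2 make them eligible for PQ. The size is at most about 48 to 240 people in the intervention arm. It rests on the assumed 2% to 10% prevalence, the planned mean cluster size and the all-residents denominator.

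The index-case mismatch is real but smaller, since three places in the text include the index case or its household and only the table wording leaves them out. The CQ exclusion is a drafting fault with one workable reading. The safety concern belongs to the first item alone. Nothing here shows that anyone has been or will be treated wrongly, and this review takes no position on which clinical rule should apply.

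**What to change.** Reconcile the abstract, the text under fMDA in the intervention arm, Table 1 and Table 2 into one eligibility table:

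- Age group by G6PD category, with the drug or none in each cell, as decided by the sponsor's clinicians.
- The index case and the members of the index household stated explicitly as in or out.
- The CQ exclusion reworded so that it can be read in only one way.

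Use that table in the field forms, in the definition of protocol-conforming delivery for the per-protocol analysis, and as the denominator for coverage. Recruitment has begun, so also record which rule the field forms have applied in any rounds already delivered.

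The cost is a clarifying amendment and a check of the field forms. No extra data, sample size or change to the primary analysis is needed.

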**Chloroquine (CQ)**					
3-day CQ (Rounds 1a, 2a, 3a)	150 mg base	Take with food to minimize possible gastrointestinal irritation	Kronos Lab, Guayaquil, Ecuador	Dose ~10 mg/kg (D1, D2), ~5 mg/kg (D3)	Dose ~10 mg/kg (D1, D2), ~5 mg/kg (D3)
sdCQ (Rounds 1b, 2b, 3b)				Dose ~10 mg/kg once	Dose ~10 mg/kg once
**Tafenoquine (TQ)** (all Rounds)	150 mg	TQ should be taken with food to increase absorption	Piramal Pharma Ltd, Mumbai, India	300 mg once	n/a
**Primaquine (PQ) **(all Rounds)	15 mg	Take with food	Colompack S.A., Bogota, Colombia	Dose ~0.5 mg/kg daily x 7 days (If TQ is contraindicated)	Dose ~0.5 mg/kg daily x 7 days
*fMDA: focal mass drug administration; CQ: chloroquine; sdCQ: single dose chloroquine; TQ: tafenoquine; PQ: primaquine; D1: Day 1; D2: Day 2; D3: Day 3* **The commercial name of the product and the manufacturer may vary depending on if the product is bought or donated.*					

Coverage and effectiveness of MDA can be compromised by drug eligibility criteria and potential challenges of acceptability, drug efficacy, adherence, imperfect surveillance to identify high-risk individuals, and human movement. Additional rounds of MDA may be needed, particularly in tropical settings where strains cause more frequent relapses in patients. Thus, the fMDA intervention will include second annual rounds (referred to as 1b, 2b, and 3b for years 1, 2, and 3, respectively). 

The regimen will include single-dose CQ (10 mg/kg × 1) with either PQ (0.5 mg/kg/day × 7 days) or TQ (300 mg × 1). CQ, including in a single dose, may potentiate the anti-relapse effect of PQ and TQ [7, 51, 52]. A single dose in the second annual rounds will also facilitate administration and acceptability. Administration of this second round at approximately 2 months after each first annual round will serve to prolong the anti-relapse, as well as providing prophylactic and transmission-blocking activity of fMDA. In multi-site, double-blind, double-dummy, randomized trials comparing TQ to placebo and to PQ [31, 36], efficacy to prevent recurrences was 72.8% (95% CI 65.6–78.8) and 67% (95% CI 61.0–72.3) for PQ and TQ, respectively, at 180 days.

#### Safety

Adverse events (AE) include any unfavorable or unintended sign, symptom, disease, syndrome, abnormal laboratory finding, or illness that emerges or worsens relative to each participant’s pre-treatment baseline, whether or not it is connected to the study intervention. Study clinicians will assess and grade all AEs based on the DAIDS severity grading scale [53]. AEs will be monitored passively, by participant calls to study staff or visits to a local health facility, and actively, through study staff who will actively inquire about AE at monthly visits.

Lack of drug tolerability will be assessed as missed doses due to vomiting or non-adherence due to adverse effects. An AE of special interest (AESI) in this study is 8-aminoquionline-associated hemolysis which is known to occur in individuals with G6PD deficiency and with malaria itself. Monitoring for this AESI and other adverse reactions will be conducted through passive and active surveillance being conducted in both study arms. Additionally, active pharmacovigilance will occur as study staff inquire about symptoms among during return visits to complete treatment. After receipt of fMDA Round 1a, Hb and urine testing will be conducted on the same day between days 3 and 7 post first treatment with either PQ or TQ [8]. Hb testing will be conducted using the Hemocue portable spectrophotometer per manufacturer’s instructions [8]. Participants and their caretakers will be made aware of possible AE and associated potential symptoms. They will be instructed to act without delay given the possible severity of some events.

For hemolytic events or other severe AEs, participants will be transported within 4 h to the hospital in Iquitos where blood transfusion therapy and other tertiary care is available. Any participant that has any severe adverse reaction associated with any study drug will be withdrawn from receiving further study drug. The participant will continue to be followed as per protocol except will not receive any additional doses of study medication.

#### Identification of index cases and measurement of incidence

Malaria case information is recorded in fever books at health posts, and these cases are reported to the regional level. Index cases from the 2 years prior to trial launch and prior to each cycle of study medication administration will be geo-located prior to that cycle. Index cases also include cases detected during regular interventions by the health system and asymptomatic cases identified during study surveys.

During the trial, any participant with a fever will be instructed to seek medical care. For any new or relapse malaria cases diagnosed, a finger prick will be obtained to collect a DBS before administering treatment. A study team member will also conduct a case investigation (within 48 h of diagnosis) to confirm clinical and demographic details. If a pre-treatment sample was not obtained, study staff will aim to collect a sample from the participant within 3 days. If the new index case is an enrolled participant in the intervention arm, they will be eligible for fMDA at the beginning of the next cycle.

The primary outcome measure of cumulative incidence is the number of incident symptomatic microscopy-confirmed *P. vivax* malaria cases in residents divided by the total population. Cumulative cases will be calculated during the period from trial launch through 1 year after the launch of round 3a of fMDA. The denominator will include all the participants in the study except for those who have withdrawn from the study.

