### Aims and objectives

The overall study objective is to evaluate the impact and safety of fMDA for *P. vivax* transmission reduction compared to no fMDA. The primary aim is to determine the effect of fMDA on the outcome of cumulative incidence of symptomatic, microscopy-confirmed *P. vivax* cases over the study period. *P. vivax* incidence will be determined based on the number of laboratory-confirmed, locally acquired cases reported from health facilities serving the catchment area of study villages. Secondary outcomes include incidence of *P. falciparum* or *P. vivax* and *P. falciparum* and infection prevalence and seroprevalence of *P. vivax* and/or *P. falciparum* measured in cross-sectional surveys (Table S1). Secondary aims are to assess the safety, tolerability, and acceptability of fMDA, as well as its cost-effectiveness compared to current standard-of-care interventions. Safety and tolerability outcomes will be measured as incidence of adverse events detected through active and passive pharmacovigilance and vomiting after administration. Acceptability will be measured as refusal rates and reported willingness to participate in future fMDA campaigns. Cost-effectiveness will be measured as cost per case averted, or per disability adjusted life year (DALY) averted. We hypothesize that fMDA will result in a greatly reduced latent hypnozoite reservoir and that will translate to reduced incidence, infection prevalence, seroprevalence, and cost-effectiveness compared to standard interventions and that it will be safe, well-tolerated, and acceptable to the community.

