#### Interim and endline cross-sectional surveys

An interim survey in a sample of the enrolled population will be performed prior to the second fMDA cycle where participants are surveyed house to house. From the list of households enrolled at the time of the survey, a random sample of households will be selected proportional to cluster size. The final study year will conclude with an endline survey in all clusters. The goal of the surveys will be to invite new or unenrolled community members to enroll in the study to include a larger proportion of the population in the study, update demographic and clinical data from enrolled participants, and collect DBS to assess secondary trial outcomes of infection prevalence and seroprevalence. Acceptability of fMDA will also be assessed in the intervention arm. Acceptability will be assessed both quantitatively and qualitatively, in terms of refusal rates and open-ended questions in the intermediate and endline surveys.

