### Statistical analysis

#### Primary analysis

An intention-to-treat (ITT) approach will used, in which all clusters with at least one index case during follow-up will be analyzed according to their randomized intervention assignment. For the primary outcome of cumulative incidence of all microscopy-confirmed cases reported in study area residents, negative binomial regression using generalized linear models with cluster-level case counts and cluster population size as an offset will also be used to estimate cumulative incidence ratios (CIR) between study arms [70, 71]. The primary analysis will adjust for covariates used in the restricted randomization (baseline incidence, population size, distance to Iquitos, and distance to a health post) [72]. We will also perform a secondary adjusted analysis that controls for covariates used in the restricted randomization as well as baseline covariates (e.g., baseline coverage of vector control interventions) that are correlated with the outcome (likelihood ratio test *p*-value < 0.2). The secondary adjusted analysis may yield higher precision than models only adjusted for restricted randomization covariates due to any chance imbalances in baseline covariates that are associated with the outcome [73]. Comparisons of incidence measures will be expressed at the cumulative incidence ratio (CIR) or the protective efficacy (PE = 1-CIR × 100%) with their corresponding 95% confidence intervals.

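### The primary outcome is defined inconsistently: several denominators and different case definitions are stated, and one pairing can bias the incidence ratio

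*Protocol article*

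**What the plan says.** All references are to the protocol article.

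**Denominator**

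- *Identification of index cases and measurement of incidence* gives symptomatic, microscopy-confirmed "malaria cases in residents divided by the total population".
- The same paragraph ends: "The denominator will include all the participants in the study except for those who have withdrawn from the study".
- *Primary analysis* fits a negative binomial model with "cluster-level case counts and cluster population size as an offset".

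**Numerator**

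- *Aims and objectives* first names symptomatic, microscopy-confirmed P. vivax cases. It then says incidence will be based on "laboratory-confirmed, locally acquired cases reported from health facilities serving the catchment area of study villages".
- *Identification of index cases and measurement of incidence* keeps symptomatic and microscopy-confirmed, with no limit on where the infection was acquired.
- *Primary analysis* counts "all microscopy-confirmed cases reported in study area residents", with neither a symptomatic nor a local-acquisition condition.

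**Participants versus residents**

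Table 1 makes enrolment depend on signed consent, age of at least 6 months and a recent night in the community. The interim and endline surveys are meant to "invite new or unenrolled community members to enroll in the study". *Trial status* keeps enrolment open until the trial ends in May 2026.

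**The concern.** A ratio of cases to people needs both counts taken from the same population. If cases come from all residents and the denominator from consenting, non-withdrawn participants, a case in an unenrolled or withdrawn resident has no matching person below the line. Someone first enrolled at the endline survey would count in full despite having contributed almost no follow-up as a participant.

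Withdrawal and late enrolment occur after allocation in an open-label trial in which only one arm is offered drug, so the participant share could differ between arms. Removing people who withdraw also sits badly with the stated intention-to-treat approach.

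On the numerator, local cases only and all cases are different endpoints. The article plans genotyping to classify infections as local or imported (*Molecular methods*) but does not say whether that classification enters the primary outcome. With the definitions unsettled, the primary analysis could be chosen after the data are seen.

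**Working it through.** **1. The plan's own figure.** Inputs from *Sample sizes and power calculations*: 15 clusters per arm, mean population 251, control rate 65 per 1000 per year, 68% reduction, k = 0.87, two-sided alpha 0.05, 3 years. Then L0 = 0.065, L1 = 0.065 × 0.32 = 0.0208, and y = 251 × 3 = 753 person-years per cluster. The Hayes-Bennett formula for unmatched clusters is

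c = (z_α/2 + z_β)² × [(L0 + L1)/y + k²(L0² + L1²)] / (L0 − L1)², plus 1 in the version with a small-sample correction.

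- (L0 + L1)/y = 0.0858/753 = 0.000114
- k²(L0² + L1²) = 0.7569 × 0.004658 = 0.003525
- (L0 − L1)² = 0.0442² = 0.001954
- c = 7.849 × 0.003639/0.001954 = 14.6 clusters per arm, or 15.6 with the extra cluster

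Power at 15 per arm is 81.0% without the extra cluster and 78.3% with it. The stated 80% is reproduced, so the point concerns what is estimated and not the power figure.

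**2. Effect of the participant denominator on resident cases.** Let c0 and c1 be the enrolled, non-withdrawn shares of residents in control and intervention. Each arm's apparent incidence is its true incidence divided by its share, so

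CIR observed = CIR true × (c0/c1).

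In a log-link model with the participant count as offset, this shifts the arm coefficient by log(c0/c1) when the share is constant within an arm. The article gives neither share, so the values below are assumed.

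| c0 | c1 | c0/c1 | CIR if truly 1.00 | CIR if truly 0.32 |
|---|---|---|---|---|
| 0.90 | 0.90 | 1.000 | 1.00 | 0.320 (68%) |
| 0.75 | 0.90 | 0.833 | 0.83 (17% apparent efficacy) | 0.267 (73%) |
| 0.90 | 0.75 | 1.200 | 1.20 | 0.384 (62%) |
| 0.90 | 0.80 | 1.125 | 1.13 | 0.360 (64%) |

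The null case with the plan's numbers: each arm has 15 × 251 = 3765 residents and, at 0.065 × 3 = 0.195, about 734 cases. Control reads 734/(0.75 × 3765) = 0.260, intervention reads 734/(0.90 × 3765) = 0.217, and the ratio is 0.83 although nothing differs between the arms.

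**3. Matched populations.** With residents in both places, or the enrolled cohort in both places, the factor c0/c1 disappears from the calculation.

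**4. Case definitions side by side.**

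| Section | Symptomatic | Locally acquired only |
|---|---|---|
| Aims and objectives | yes | yes, in the sentence on how incidence is determined |
| Identification of index cases and measurement of incidence | yes | no |
| Primary analysis | not stated | no |

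The article gives no imported share, so no size is attached to this part.

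**The case against.** The strongest reply is that the participant denominator appears in one sentence only. The outcome is first put over the total population, the model that produces the CIR uses cluster population size, and *Potential challenges* says monthly household visits will keep population estimates accurate. On that reading the sentence is a slip and the offset governs. This stands as far as it goes: a reader might infer that the plan has settled on participants as the denominator, and it has not. But the sentence's exclusion of withdrawals makes sense only for enrolled people, so it is a distinct rule and not loose wording for residents.

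The scope for unequal shares is also narrower than it may look. *Study design* lists enrolment before allocation, and *Enrollment and a baseline assessment* places it before any intervention. Consent to drug is sought separately, so refusing drug does not require leaving the study, and people stopped from drug after a severe reaction remain in follow-up. What remains is withdrawal and late enrolment, and the 15-point gap used above is illustrative.

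Three stronger inferences on the numerator are not supported:

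- **Imported cases cost the trial its power.** The power statement attaches the 68% to cumulative P. vivax incidence with no local limit. A loss appears only if the 68% is reassigned to local cases and an imported share is supplied.
- **fMDA cannot affect imported infections.** The article describes tafenoquine prophylaxis lasting up to 77 days and treatment of hypnozoites, which is not confined to locally acquired infection.
- **Staff aware of the arm will judge case origin.** The only classification method described is genotyping, and the statistician and analyst are blinded.

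Laboratory-confirmed in the aims is not a separate endpoint either, since the sentence before it specifies microscopy.

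**Conclusion.** The concern holds as an inconsistency in the definition of the primary outcome. One paragraph gives two denominators, the analysis section words the offset as cluster population size, and the three sections disagree on local acquisition and on whether cases must be symptomatic. This rests on the text alone.

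The bias is conditional. It arises only if the participant denominator is applied to resident cases and the enrolled, non-withdrawn shares differ between arms. It can go in either direction and is zero when the shares are equal. The size depends entirely on assumed shares: at 0.75 and 0.90, 17% apparent efficacy under no effect. Because it affects the primary estimate and could be resolved after the results are known, it should be settled before data are examined by arm.

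**What to change.** State one matched pair in *Aims and objectives*, *Identification of index cases and measurement of incidence* and *Primary analysis*:

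- **Numerator:** symptomatic, microscopy-confirmed P. vivax cases in all census residents, enrolled or not, wherever acquired.
- **Offset:** the updated census resident population of the cluster, with no removal for withdrawal and a stated rule for counting people who move in or out.

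Delete the sentence that defines the denominator as participants minus withdrawals. Remove the local-acquisition limit from the aims and restore the symptomatic condition in the analysis section. Report locally acquired cases only as a sensitivity analysis, classified blind to arm. If cases in non-enrolled residents cannot be used, restrict both numerator and denominator to the enrolled cohort and say so.

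A person-time offset would also be acceptable, but that is a preference and the correction does not need it.

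The cost is wording. The census and monthly population updates are already planned, and the sample size is unaffected.
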